## Abstract

**Background::**

Mycoplasma pneumonia is a common disease in pediatrics, and macrolides is the first choice for the treatment. However, the increase of antibiotic resistance of macrolides makes it more and more complicated for clinical treatment. Due to the long term treatment of macrolides, it may increase the incidence of nausea, vomiting, abdominal pain, diarrhea, and other gastrointestinal symptoms, vascular phlebitis, liver and kidney function damage. Tanreqing injection, a Chinese herbal extraction injection, has advantages in the treatment of mycoplasma pneumonia in children, and it could improve the curative effect, shortening the course of disease, and reducing the side effects. Yet there is a lack of standard clinical studies to verify it, so this randomized controlled trial (RCT) will evaluate the efficacy and safety of Tanreqing injection combined with azithromycin in the treatment of mycoplasma pneumonia in children.

**Methods::**

This is a prospective RCT to study the efficacy and safety of Tanreqing injection combined with azithromycin in the treatment of mycoplasma pneumonia in children. It is approved by the Clinical Research Society of our hospital. According to the 1:1 ratio, the patients will be randomly divided into Tanreqing injection combined with azithromycin group (observation group) and azithromycin group (control group). Duration of hospitalization, clinical improvement 7 days after admission, changing laboratory tests, pulmonary function, immunoglobulin level, and adverse reactions will be compared between the 2 groups. The data will be analyzed by SPSS 16.0 software.

**Discussion::**

This study will evaluate the efficacy and safety of Tanreqing injection combined with azithromycin in the treatment of mycoplasma pneumonia in children. The results of this experiment will provide clinical basis for the treatment of mycoplasma pneumonia in children with Tanreqing injection combined with azithromycin.

**Trial registration::**

OSF Registration number: DOI 10.17605/OSF.IO/X6VFS.

## Introduction

1

Mycoplasma pneumonia (MP) is one of the common respiratory diseases in clinic, which mainly occurs in children and adolescents. The main clinical manifestations are fever, cough, and lung rale.^[1]^ In recent years, the number of pediatric patients infected with Mycoplasma pneumoniae is increasing year by year, and showing a younger trend.^[2]^ According to the survey, MP accounted for 10% to 40% of hospitalized children with community-acquired pneumonia.^[3]^ Because of the serious side effects of tetracycline and fluoroquinolones on children, macrolides have become the first choice for the treatment of mycoplasma pneumonia in children.^[4,5]^ Azithromycin (a macrolide antibiotic) is the first choice, which has a long half-life and obvious effect on target cells.^[6]^ It has the advantages of strong inhibition to mycoplasma, little damage to liver and kidney function, and little stimulation to stomach. However, the increase of antibiotic resistance of macrolides makes it more and more complicated for clinical treatment,^[7,8]^ also, the long term treatment of azithromycin may increase the incidence of nausea, vomiting, abdominal pain, diarrhea and other gastrointestinal symptoms, vascular phlebitis, so it is necessary to seek new alternative treatments.

Traditional Chinese medicine injection is made of ingredients extracted from Chinese herbal medicine by modern technology, which has the characteristics of rapid action and high bioavailability.^[9]^ It has been confirmed that traditional Chinese medicine injection combined with azithromycin in the treatment can improve the efficacy and safety of MP in children.^[10]^ Tanreqing is a traditional Chinese medicine injection extracted from Scutellaria baicalensis, bear bile powder, goat horn, honeysuckle, and forsythia suspense. It has the effect of reducing fever, resolving phlegm, and relieving cough. It can not only inhibit a variety of viruses and bacteria, but also regulate immune function and enhance immunity.^[11]^ Its efficacy and safety have been confirmed in influenza, lung infection, and other diseases.^[11,12]^ Tanreqing injection has been used in the treatment of mycoplasma pneumonia in children for many years, and it could improve the curative effect, shortening the course of disease, and reducing the side effects of Azithromycin.^[13]^ However, there is no strict randomized controlled trial (RCT) to study the efficacy of Tanreqing injection combined with azithromycin in the treatment of MP in children. Therefore, we intend to use this RCT to evaluate the efficacy and safety of Tanreqing injection combined with azithromycin in the treatment of mycoplasma pneumonia in children.

## Materials and methods

2

### Study design

2.1

This is a single center, prospective RCT to study the efficacy and safety of Tanreqing injection combined with azithromycin in the treatment of mycoplasma pneumonia in children. The study will be based on the SPIRIT Randomized study list, follow the Consolidated Standards of Reporting Trials, and provide Consolidated Standards of Reporting Trials flow charts (Fig. 1).

**Figure 1 F1:**
[figure not shown]
Flow diagram.

### Ethics and registration

2.2

This research scheme is in line with the Helsinki Declaration and approved by the Clinical Research Ethics Committee of our hospital. This experiment has been registered in the open science framework (OSF) (registration number: DOI 10.17605/OSF.IO/X6VFS). Before the beginning of the study, we will fully inform the family members of the patients about the purpose, method and potential risks of this study, and sign a written informed consent form after obtaining their consent. They are free to choose whether to continue the experiment at any time during the study.

### Patients

2.3

Inclusion criteria:

1.meet the diagnostic criteria of mycoplasma pneumoniae pneumonia in children, age ≤15 years old;2.have obvious clinical symptoms of irritant cough, and chest imaging examination to support the diagnosis;3.serum mycoplasma pneumoniae specific antibody IgM test showed positive.

Exclusion criteria:

1.complicated with other respiratory tract infection;2.liver and kidney function damage;3.allergy to azithromycin or Tanreqing injection;4.unable to cooperate with health care workers to carry out relevant diagnosis and treatment in the course of treatment;5.patients with test drug allergy;6.patients with severe digestive or blood system abnormalities;7.recent treatment with immunosuppressants and other antibiotics;8.unable to understand the research scheme or unwilling to participate after explanation.

### Distribution scheme

2.4

We plan to include 120 patients who meet the requirements, which are randomly divided into the observation group and the control group according to the ratio of 1:1. Random numbers will be generated by computer software programs designed by statisticians who are not familiar with the content of the study. The random numbers assigned to each group will be written on a piece of paper and placed in a sealed and opaque envelope. Envelopes will be provided to participants in random order. The evaluators in the trial do not know the random assignment of the participants. The statistics and analysis of the data will be completed by statistical researchers who have no knowledge of the grouping.

### Intervention measures

2.5

After admission, all patients will receive symptomatic and support treatment, such as antipyretic, antitussive, expectorant, oxygen inhalation, and so on. The following treatment plan according to the group will be performed.

Control group: Azithromycin sequential therapy, give azithromycin injection, 10 mg/ (kg d) + 5% glucose injection, 100 ml to 250 ml intravenous drip, once a day. After continuous use for 3 days, stop for 4 days, and then give azithromycin dry suspension 10 mg/kg, orally, once a day for 7 days.

Observation group: on the basis of the treatment plan of the control group, Tanreqing injection will be given 0.5 ml/ (kg d) + 5% glucose injection 100 ml intravenous drip, once a day, and the daily threshold is 20 ml, for 14 days.

The distribution of drugs will be distributed by unwitting nurses to patients with corresponding numbers according to the drug number. The patients will be treated according to the corresponding treatment plan for 2 wk and followed up for 30 d. Lung function, laboratory examination, and chest imaging examination will be performed 1 week after treatment and the end of treatment.

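### Nurses described as unaware of treatment cannot remain so under the written regimens, which puts evaluator blinding at day 7 and length of stay at risk

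*Protocol article*

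**What the plan says.** On masking, the protocol article makes three statements.

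- Nurses (Intervention measures): "The distribution of drugs will be distributed by unwitting nurses to patients with corresponding numbers according to the drug number".
- Evaluators (Distribution scheme): "The evaluators in the trial do not know the random assignment of the participants".
- Analysts (Distribution scheme): the data are analysed by people unaware of the grouping.

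It does not say that patients, families or treating doctors are blinded, and it does not call the trial double-blind.

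The regimens are in the same section as the nurse statement. Control receives azithromycin as a "100 ml to 250 ml intravenous drip, once a day", followed by: "After continuous use for 3 days, stop for 4 days, and then give azithromycin dry suspension 10 mg/kg, orally, once a day for 7 days". The observation arm is an add-on: "on the basis of the treatment plan of the control group, Tanreqing injection will be given", also as a drip, "once a day, and the daily threshold is 20 ml, for 14 days". No placebo or dummy infusion is mentioned for control.

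The primary outcomes (Observation index) are length of hospital stay and clinical improvement 7 days after admission.

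**The concern.** Numbering the drugs hides the arm only if what is dispensed looks the same in both arms. Here one arm has an extra drip at first, and later has the only study drip. A nurse who handles the drugs, a parent at the bedside and a doctor on the ward can all work out the allocation without seeing the randomisation list. If the nurse statement stays, the trial will report a protection that its own regimens rule out.

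Both primary outcomes are exposed. Day-7 improvement is assessed while the arms look different, so an evaluator who sees the child on the ward may learn the arm. Length of stay depends on discharge decisions. If treating staff make these, people who can see the arm decide the outcome, and a 14-day infusion course in one arm only may itself influence when a child goes home.

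**Working it through.** **1. Check of the stated treatment length.** The article states the length in this sentence: "The patients will be treated according to the corresponding treatment plan for 2 wk and followed up for 30 d". Control: 3 intravenous days + 4 days without study drug + 7 oral days = 14 days = 2 weeks. Observation: 14 Tanreqing days. The stated figure is reproduced.

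**2. Study treatment by day, counting the first treatment day as day 1.**

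| Days | Control | Observation |
|---|---|---|
| 1-3 | one drip a day | two drips a day |
| 4-7 | no study drug | one drip a day |
| 8-14 | oral suspension | oral suspension and one drip a day |

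- Study infusions in total: control 3; observation 3 + 14 = 17.
- Up to day 7: control 3; observation 3 + 7 = 10.
- Days with a study drip in the observation arm only: 14 - 3 = 11 (days 4 to 14).
- Days with nothing to dispense to control: 4 (days 4 to 7).

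The article sets the assessment at 7 days after admission. If treatment starts on the day of admission, this may be treatment day 7 or day 8, depending on how days are counted. On both days only the observation arm has a study drip, so the conclusion does not depend on the convention.

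**3. How much a rating difference could matter (illustration).**

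Inputs from the article: 120 patients at 1:1, so 60 per arm; a chi-squared test; significance at P < 0.05.

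Assumptions: improvement is scored yes/no; the test is two-sided without continuity correction; the true improvement rate p is 60%, 70% or 80% in both arms; knowledge of the arm lifts the rated proportion in the observation arm by d and leaves control unchanged.

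With x and y improved in the two arms and m = (x + y)/120, the test statistic is z = [(x - y)/60] / sqrt[m(1 - m) × 2/60]. The false-positive rate is the sum of Bin(x; 60, p + d) × Bin(y; 60, p) over all pairs with |z| > 1.96.

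| True rate p | d = 0 | d = 5 points | d = 10 points |
|---|---|---|---|
| 60% | 0.051 | 0.087 | 0.210 |
| 70% | 0.052 | 0.098 | 0.250 |
| 80% | 0.050 | 0.107 | 0.326 |

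Hand check by normal approximation for p = 70%, d = 10 points:

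- standard error under the null: sqrt(2 × 0.75 × 0.25/60) = 0.0791
- standard error under the alternative: sqrt[(0.21 + 0.16)/60] = 0.0785
- (0.10 - 1.96 × 0.0791)/0.0785 = -0.70, which gives 0.242, close to the exact 0.250.

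In children, 5 points is 0.05 × 60 = 3 and 10 points is 6. At p = 70%, 18 of 60 are expected not to improve, so these lifts mean rating 3/18 = 17% or 6/18 = 33% of them too favourably.

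**The case against.** The strongest reply is that the nurse sentence is only one of three masking statements. Evaluators and analysts are separately said to be unaware of the allocation. Neither group needs a placebo to stay blinded, and the article never claims blinding of patients, families or treating doctors. This stands. A reader might infer that the trial has no blinding at all, but the documents do not support that: only the nurse statement conflicts with the regimens.

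The nurse sentence could also be read narrowly, as covering those who hand out numbered drugs and not those who set up the drip. This helps little. A supply with an added injection differs from one without it, and for 4 days control has nothing to hand out.

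A reader might also take the day-7 result to be biased. The article does not say where, when or by whom the assessment is made, so bias there is a risk and not a demonstrated result. The article's silence on improvement criteria and on how evaluators are kept unaware is not a fault in itself, because the full protocol may contain both.

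The size is open to challenge too. One can build a table that crosses the threshold with no true effect: 51/60 against 42/60 gives P = 0.049. But this needs 9 of 18 unimproved children (50%) misrated in one arm and none in the other, and with continuity correction P is about 0.08. The article says only that a chi-squared test is used. The smaller lifts in the working are the fairer illustration, although they too rest on assumed rates and on the uncorrected test.

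Finally, control having no drip from day 4 is true of study drugs only, because supportive care might include one. The absence of a dummy infusion is inferred from the regimens as written; the article does not state it in words.

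**Conclusion.** The concern holds in a limited form. The nurse statement and the regimens in the same section contradict each other and must be reconciled: 3 study infusions against 17, and 11 days on which only one arm has a study drip. Treatment is in effect open-label for nurses, families and treating staff, unless the full protocol describes a concealment that the article omits.

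Evaluator and analyst blinding remain achievable. Evaluator blinding is harder to keep at day 7 than the article suggests, and length of stay is exposed wherever discharge is decided by staff who can see the arm. On the assumptions stated, a 5-point rating lift roughly doubles the false-positive rate (about 5% to 9-11%), and a 10-point lift takes it to 21-33%. These figures show how sensitive the test is to such a lift. They do not estimate what will happen in this trial, and they do not apply to length of stay.

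**What to change.** 1. Delete the statement about nurses and drug numbers, or state how concealment is achieved under these regimens.
2. Describe the trial as open-label in treatment, with blinded evaluators and blinded analysts.
3. Have the existing evaluators assess day-7 improvement outside infusion time, with intravenous sites covered in both arms and no access to treatment charts, against criteria that the investigators fix beforehand. If the full protocol already contains such criteria or procedures, refer to them.
4. Report length of stay as an outcome open to discharge decisions by staff who are not blinded.

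The cost is a change of wording, minor scheduling effort for the existing evaluators, and a less favourable description of the masking. No placebo, extra staff or change to treatment is needed.

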### Observation index

2.6

1.The primary outcomes are duration of hospitalization, and clinical improvement 7 days after admission.2.The secondary outcomes are changing laboratory tests (IgA, IgG, and IgM) during 7 days, lung function, changing of CT findings after 30 days.3.Adverse reactions include gastrointestinal reactions, rash, dizziness, abnormal liver and kidney function, etc.

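### Length of stay is a primary outcome, yet only the observation arm is prescribed a daily drip for 14 days (control: 3 IV days), so stay is likely confounded by the infusion schedule

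*Protocol article*

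**What the plan says.** Section 2.6 (Observation index) of the protocol article names two primary outcomes: "The primary outcomes are duration of hospitalization, and clinical improvement 7 days after admission".

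Section 2.5 (Intervention measures) sets the regimens. Control children receive intravenous azithromycin first: "After continuous use for 3 days, stop for 4 days", and "then give azithromycin dry suspension 10 mg/kg, orally, once a day for 7 days". The observation arm is an add-on: "on the basis of the treatment plan of the control group, Tanreqing injection will be given", as a drip "once a day, and the daily threshold is 20 ml, for 14 days".

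The same section places the start of care in hospital ("After admission, all patients will receive symptomatic and support treatment") and says that patients are "treated according to the corresponding treatment plan for 2 wk and followed up for 30 d". It describes no placebo infusion for control. It does not say where infusions are given once a child is well enough to leave. Section 2.4 (Distribution scheme) says that evaluators and data analysts do not know the allocation.

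**The concern.** Duration of hospitalization counts bed days, and the assigned treatment can itself create bed days in one arm only. From day 4 the control arm has no prescribed intravenous trial drug, while the observation arm still has most of its drip course to run. The article fixes both the outcome and the schedule, and the two pull against each other, so this is more than a detail left to a fuller document. Randomisation does not remove the problem, because it arises after allocation and from the allocated schedule.

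At stake is the interpretation of the first-named primary outcome. If some observation children stay in to finish their drips, a true speeding of recovery could be diluted, cancelled or turned into an apparently longer stay. If they leave on recovery instead, the regimen tested is shorter than the one prescribed, or is continued somewhere unspecified.

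**Working it through.** **1. Intravenous days, from section 2.5, taking the Tanreqing course to start with azithromycin on day 1.**

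| Days | Control | Observation |
|---|---|---|
| 1–3 | IV azithromycin | IV azithromycin + IV Tanreqing |
| 4–7 | no azithromycin | IV Tanreqing |
| 8–14 | oral azithromycin | oral azithromycin + IV Tanreqing |
| Total IV days | 3 | 14 |

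The difference is 14 − 3 = 11 days.

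**2. What can happen to an observation child who recovers before day 14.**
- The course is completed in hospital: stay is about 14 days, regardless of recovery.
- The child is discharged on recovery and the drip stops: the outcome event cuts the intervention short.
- The drip continues outside the ward: the article does not mention this, and discharge may then depend on whether daily infusion can be arranged, a constraint that only one arm has.

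In the first case stay does not measure recovery. In the other two it is entangled with the regimen.

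**3. Break-even share.** The article states no mean stay, SD, benefit or retained share, so there is no figure of its own to reproduce and the inputs here are assumptions. Let m be the control mean stay, b the true benefit in days and p the share of observation children kept to day 14, unrelated to how fast they recover. The observation mean is (m − b)(1 − p) + 14p. Setting this equal to m gives p = b / (14 − m + b).

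| m (days) | b = 1 | b = 2 |
|---|---|---|
| 8 | 1/7 = 14% | 2/8 = 25% |
| 10 | 1/5 = 20% | 2/6 = 33% |
| 12 | 1/3 = 33% | 2/4 = 50% |

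Above these shares the mean difference points the wrong way.

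**4. Effect on the test.** Simulation with 60 per arm (120 randomised 1:1, section 2.4), Mann–Whitney test (section 2.8) at two-sided 0.05 (sidedness assumed), 1,000 runs per setting. Assumed: control mean 7 or 10 days, SD 2, 3 or 4, minimum stay 3 days. Ranges run over these six settings.

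| Share kept to day 14 | No true benefit: stay significantly longer | True benefit 2 days: stay significantly shorter | True benefit 2 days: stay significantly longer |
|---|---|---|---|
| 0% | 2–3% | 73–99.9% | 0% |
| 10% | 11–18% | 31–94% | 0% |
| 25% | 40–67% | 3–34% | 0–6% |
| 50% | 93–99.8% | about 0% | 50–89% |
| 100% | 100% | 0% | 100% |

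With everyone kept in and no true benefit, the observation arm stays about 4 to 7 days longer, which agrees with 14 − 10 = 4 and 14 − 7 = 7.

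**5. Sensitivity to the inputs.** With mean 10, benefit 2 and 15% kept in, the observation mean is 8 × 0.85 + 14 × 0.15 = 8.9 days. The difference is still −1.1 days. With mean 8 and benefit 1, the same 15% gives 7 × 0.85 + 14 × 0.15 = 8.05 days, a difference of +0.05. The direction of the distortion is stable; its size depends on inputs the article does not give.

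**The case against.** The strongest reply has five parts.

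- **Inpatient bed.** The article never says that a once-daily drip requires one. Infusions given to outpatients would add no hospital days, and discharge rules may sit in a full protocol that is not shown. This stands against the absolute reading. A reader might infer that length of stay measures the infusion schedule rather than recovery; the documents support only that it is likely confounded by the schedule. Even so, a rule held elsewhere would still have to settle which of the three cases in the working applies.
- **Unblinded discharge.** A reader might also infer that the staff who decide discharge can see the arm. The article does not say who decides discharge, and it describes masked evaluators and masked drug distribution. With no placebo infusion described, unmasking is plausible, but it is an inference. The schedule problem would remain even with masked discharge decisions.
- **Control stay.** The two-week plan applies to both arms, so control stay may follow the schedule too. That would shrink the contrast. Early control discharge is an assumption.
- **Single threshold.** A break-even of 1 in 7 is tempting to quote, but it holds only for an 8-day mean and a 1-day benefit.
- **Legitimacy of actual stay.** Bed days needed to deliver an add-on infusion are a real consequence, and extra bed days would work against Tanreqing, so they would not manufacture a benefit. This is a good reason to keep reporting actual stay. It does not make stay a measure of whether recovery is faster.

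**Conclusion.** The point holds in a qualified form. As sections 2.5 and 2.6 stand, the first-named primary outcome is likely confounded by an 11-day difference in prescribed intravenous treatment. The expected direction is against the observation arm, so a true benefit could be masked or reversed.

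The size cannot be fixed from the article. Under assumed control means of 8 to 12 days and benefits of 1 to 2 days, the benefit is erased when about 14% to 50% of observation children remain to day 14 for infusions. This assumes that each such child stays 14 days and that staying is unrelated to speed of recovery. If no child is kept in for infusions, the bias in stay from that source disappears, but the question of a shortened or relocated course remains.

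The second primary outcome is assessed at a fixed day and does not share this schedule problem.

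**What to change.** Reconcile sections 2.5 and 2.6 through the outcome definition:

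- **Primary outcome.** Replace actual stay with the time from randomisation to first meeting prespecified, objective discharge-readiness criteria, applied identically in both arms whether or not infusions are continuing.
- **Scoring.** Score daily in hospital and stop once the criteria are met, so no post-discharge visits are needed for this outcome. Rely as far as possible on recorded objective signs, because a visible drip may unmask the evaluators.
- **Analysis.** Treat it as time-to-event (log-rank test, Cox model), with withdrawals and transfers censored so that they do not count as short stays. Report their numbers by arm.
- **Secondary outcome.** Keep actual length of stay, reported with the number of Tanreqing infusion days each child received.

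The cost is one amended outcome definition and a daily checklist, with no extra patients. No change to the treatment schedule is proposed.

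### No listed assessment supplies the secondary outcome of CT change after 30 days: the last listed chest image falls 9 to 30 days earlier, and the modality is not aligned

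*Protocol article*

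**What the plan says.** Section 2.6 (Observation index) lists among the secondary outcomes "changing of CT findings after 30 days". It does not say whether the 30 days run from admission, from the start of treatment or from its end.

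Section 2.5 (Intervention measures) sets the on-study imaging: "Lung function, laboratory examination, and chest imaging examination will be performed 1 week after treatment and the end of treatment". The sentence before it says that patients will be "treated according to the corresponding treatment plan for 2 wk and followed up for 30 d", and no assessment is named for that follow-up.

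Section 2.3 (Patients) requires at entry a "chest imaging examination to support the diagnosis", so some chest image exists at baseline, but its type is not given. CT appears in the outcome and in neither of the other two places.

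**The concern.** The article states both when the outcome is to be assessed and when images are to be taken, and the times do not match. A team that follows section 2.5 as written has no planned image from which to derive the outcome in section 2.6.

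Two things are at stake. First, an image not taken at the right time cannot be recovered at analysis. The outcome would then rest on whatever unscheduled scans happened to exist, or an end-of-treatment image would be reported under a 30-day label. Secondly, a change needs comparable images at both ends. If the entry image is of another type than the later one, a difference between them may reflect the examination and not the disease.

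**Working it through.** This is a timeline check; no sample size, power or event count enters. The article gives no figure of its own to reproduce. Days are counted from the start of treatment, which is assumed to coincide with admission.

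**Step 1: end of treatment.**
- Control arm, section 2.5: "After continuous use for 3 days, stop for 4 days, and then give azithromycin dry suspension 10 mg/kg, orally, once a day for 7 days". Length = 3 + 4 + 7 = 14 days.
- Observation arm, section 2.5: "the daily threshold is 20 ml, for 14 days". Length = 14 days.
- Both agree with the stated two weeks, so the end of treatment is day 14 in both arms.

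**Step 2: listed imaging times.** One is the end of treatment, day 14. The other can be read in two ways:
- one week after treatment starts: day 7, so the last listed image is on day 14;
- one week after treatment ends: 14 + 7 = day 21, so the last listed image is on day 21.

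**Step 3: outcome time.**
- 30 days from admission or start: day 30.
- 30 days from end of treatment: 14 + 30 = day 44.

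**Step 4: gap = outcome day − last listed image day.**

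| Last listed image | Outcome at day 30 | Outcome at day 44 |
|---|---|---|
| Day 14 | 30 − 14 = 16 days | 44 − 14 = 30 days |
| Day 21 | 30 − 21 = 9 days | 44 − 21 = 23 days |

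The gap is between 9 and 30 days and is zero in no cell. If the first imaging time means day 7, as its being named before the end of treatment suggests, the gap is 16 or 30 days.

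**Step 5: modality.** Outcome (2.6): CT. Schedule (2.5): chest imaging. Entry criterion (2.3): chest imaging. Nothing in the article ensures that the entry image, or either on-study image, is a CT.

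**The case against.** The strongest reply is that the follow-up and the outcome share the same 30-day interval, so the CT was probably meant to belong to that follow-up. Section 2.5 does not say that its two imaging times are the only ones, journal articles often leave visit tables to the full protocol, and the flow diagram (Figure 1) is not available here. This stands in part. A reader might infer that the outcome will never be measured, or that none of the 120 planned children will have a 30-day CT. The article does not support that, because it does not exclude imaging during follow-up. What it supports is that no listed assessment supplies the outcome. The reply does not remove the conflict: the article is not silent on imaging but gives explicit times, and these differ from the time in the outcome.

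A reader might also infer that any 30-day scans would come mainly from children who are not recovering, and would differ by arm. That could happen if scans were left to clinical need, but no section says they would be, so no bias of that kind is claimed here.

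Nor can it be said that the listed images serve no purpose. The primary outcome of clinical improvement at 7 days is not defined in the article and might draw on an early image, and earlier images can show the course of the CT findings.

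Finally, this is one secondary outcome among several. The primary outcomes and the adverse-reaction assessment do not rest on it. That argues for a lower severity, not for leaving the text as it is.

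**Conclusion.** The concern holds as a conflict between sections 2.5 and 2.6. The last listed chest image, on day 14 or day 21, falls 9 to 30 days before the outcome time of day 30 or day 44, and no reading reconciles them. The outcome also names a modality that neither the schedule nor the entry criterion names.

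This rests on two assumptions: that treatment starts at admission and runs its stated 14 days, and that the article's text is complete on imaging. The full protocol or the flow diagram may list a 30-day scan. Even then, the article's schedule would need correcting to show it.

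The severity is should-fix. The text is wrong as written and an image not taken cannot be recovered later, but the primary comparison is unaffected.

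**What to change.** Before enrolment, reconcile sections 2.5 and 2.6 so that both name the same time point, the same modality and the day from which time is counted, including the origin of the 30-day follow-up and of the one-week imaging time. The documents do not show which time was intended, so the sponsor must choose between two routes:

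- **End of treatment.** Define the outcome as change in chest imaging from admission to end of treatment. Compare like modality with like, and have the images assessed without knowledge of assignment. Section 2.4 already keeps the evaluators unaware of allocation, but does not say that they read the images, so this should be stated. The cost is a short change of wording and no added visit. Because the modality is open at present, like-with-like comparison may restrict which examination is used at entry or at the end. The downside is that no claim can be made about resolution at 30 days.
- **30 days.** If the later time was intended, list the imaging in section 2.5 for all children at the 30-day follow-up, with the modality matched to the entry image. This keeps the stated outcome. The cost is one further listed examination per child, up to 120 across the trial.

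Under either route the imaging time should be fixed for every child, so that the outcome does not depend on who happens to be scanned.
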